#### Chemotherapy completion rates

Chemotherapy completion rate will be assessed as the average relative dose-intensity for the originally planned regimen based on standard formulas [41]. The data will be obtained via medical records.

#### Costs from a societal perspective

For cost-utility purposes, the EQ-5D, a brief HRQoL measurement, is included in the questionnaire package [42]. Health care costs, patient and family costs, and production losses will be assessed, and relevant data will be collected thought retrospective cost diaries measured on a monthly basis during the entire study period.

### Sociodemographic and clinical data

At baseline, sociodemographic data (e.g., age, gender, education, marital status, living and work situation), and lifestyle variables (e.g., smoking history), are being obtained via questionnaire.

Clinical information, including (date of) diagnosis, tumor characteristics, treatment (e.g., type of surgery, chemotherapy regimen), hemoglobin levels and medication use will be abstracted from the medical records. During the follow-up period, data on disease status (progression/recurrence) and any additional treatment (e.g., endocrine therapy, trastuzumab) is obtained via medical records and self-report.

### Moderating variables

A series of questions is posed to assess potential moderating variables, and variables that may be predictive of compliance with the physical exercise and activity programs. These include items assessing attitudes towards and beliefs about physical activity, social influence from peers, barriers to and perceived benefits of physical activity, self-efficay towards physical activity and stage of change [43-46]. Patients' preferences for type of exercise intervention is also being assessed [21].

### Non-participant analysis

In previous studies of exercise programs among patients with cancer, the generalizability of the results was limited due to a relatively low participation or uptake rate [13,14]. We expect that, in the current trial, a substantial percentage of eligible patients will decline the invitation to participate in the trial. We hypothesize that patients who choose not to participate have been less physical active and have led a more sedentary lifestyle prior to becoming ill than those who participate. We also expect that they have less favorable attitudes towards physical exercise, in general, and during chemotherapy treatment, in particular. Sociodemographic characteristics, fatigue and attitudes and behaviors with regard to physical exercise of the non-participants will be compared with those of the trial participants, using appropriate statistics (e.g. students t-test, chi square, etc.).

### Power calculation

The primary study outcomes include two performance measures (cardiorespiratory fitness and muscle strength) and self-reported fatigue. It is expected that patients in the usual care condition will experience a 5%-10% decline in physical fitness during their chemotherapy treatment, that this will improve gradually during the post-treatment period, but will not necessarily return to pretreatment levels. It is hypothesized that the OnTrack program will yield at least a 20% improvement in general physical fitness. Based on the results of Courneya et al., a pretreatment mean for the 1-repetition maximum for leg extension is estimated to be 25 kg, with a standard deviation of 12 kg [15]. We expect that the Onco-Move program will help patients to maintain their pretreatment levels of cardiorespiratory fitness, but not necessarily improve, and that it will have little or no effect on muscle strength.

Based on the above figures, 100 patients per group are needed to detect a 0.40 standard deviation difference (Cohen's effect size [47]) in performance-based outcomes between the OnTrack group and the usual care group at the post-chemotherapy assessment, with power set at 0.80 and alpha at 0.05 (two-sided test).

We will recruit 360 patients into the trial to allow for an attrition of approximately 20% (i.e., patients who discontinue participation in the trial entirely, including failure to complete follow-up assessments). These numbers will be sufficient to detect a one-half standard deviation unit difference in self-reported fatigue. This magnitude of difference is generally considered to be indicative of clinically meaningful differences in patients' self-reported symptom experience [47,48].

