### Primary outcome measures

#### Cardiorespiratory fitness

Cardiorespiratory fitness is being assessed with the steep ramp test (an incremental bicycle ergometer test) and a cycle endurance test. Both tests are completed on a calibrated, electronically-braked cycle ergometer (Corival, Lode, Groningen, The Netherlands). For the steep ramp test, the patient is instructed to cycle at a speed between 70 and 80 revolutions per minute (RPM), starting with a 3 minutes warming-up at 10 Watts. The test starts at 25 Watts, after which the load is increased by 25 Watts every 10 seconds. The test ends if cycling speed falls below 60 RPM. Maximal workload (Wmax), time cycled at that load, and heart rate at the end of the test are recorded. The steep ramp test has been shown to be a reliable (ICC = 0.996) and valid (correlation with peak oxygen uptake (peakVO_2_) of 0.85) means of estimating maximal workload in patients with cancer. PeakVO_2 _can be estimated from the steep ramp test using a linear regression equation [33].

Exercise endurance is measured after a period of rest following the steep ramp test. The cycle endurance test is done at a workload based on 70% of the Wmax reached during the steep ramp test. After a one-minute warming-up on the same ergometer that was used for the steep ramp test, the load is increased to the predetermined workload. The patient continues cycling at this constant submaximal workload until the cycling speed falls below 60 RPM, with a maximum time of 30 minutes. The endurance time and heart rate at the end of the test are recorded. The workload of the endurance test used at follow up measurements is the same as that of the baseline endurance test.

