#### Fatigue

Fatigue symptoms are assessed with the Multidimensional Fatigue Inventory (MFI) [38]. The MFI is composed of 20 items, organized into five scales: general fatigue, physical fatigue, reduced activity, reduced motivation, and mental fatigue. Questions are posed about the past few days, and responses are recorded on a five-point scale.

In addition to the MFI patients are asked to complete the Fatigue Quality List (FQL) [39], assessing patients' perception and appraisal of experienced fatigue. The FQL consists of 25 adjectives describing the fatigue experience, organized into 4 subscales: frustrating, exhausting, pleasant, and frightening.

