**Primary Outcome measures**	

Cardiorespiratory fitness	Steep Ramp Test [33] Endurance Test

Upper Muscle Strength	JAMAR^® ^grip strength dynamometer [34] microFET^® ^HHD elbow flexion [35]

Lower Muscle Strength	microFET^® ^HHD extension knee [36] 30 s chair stands test [37]

Fatigue	MFI [38] FQL [39]

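### Three named primary outcomes unfold into 15 equally ranked primary scores, while the sample size rests on a single two-sided 0.05 test

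*Protocol article*

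**What the plan says.** The Power calculation section of the protocol article names three primary domains: "The primary study outcomes include two performance measures (cardiorespiratory fitness and muscle strength) and self-reported fatigue". It sizes the trial for OnTrack against usual care at the post-chemotherapy assessment, for a difference of 0.40 SD, "with power set at 0.80 and alpha at 0.05 (two-sided test").

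The sections under the primary outcome heading, together with Table 1, expand the three domains:

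- Cardiorespiratory fitness is "assessed with the steep ramp test (an incremental bicycle ergometer test) and a cycle endurance test".
- Upper-limb strength in Table 1 is measured by "grip strength dynamometer [34] microFET" (the latter for elbow flexion), and lower-limb strength by "extension knee [36] 30 s chair stands test [37".
- Fatigue is measured by the MFI, "organized into five scales: general fatigue, physical fatigue, reduced activity, reduced motivation, and mental fatigue", and by the FQL, "organized into 4 subscales: frustrating, exhausting, pleasant, and frightening". Table 1 lists both instruments as primary.

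The Background section closes with hypotheses for each program against usual care and for OnTrack against Onco-Move. Study outcomes sets post-baseline assessments at the end of chemotherapy (T1) and at six months (T2). Statistical analyses plans two methods for the performance outcomes, a multilevel regression of percentage change and a group-by-time repeated-measures MANOVA of mean scores, and does not say which decides. The self-report scores get the MANOVA.

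**The concern.** A trial sized on one test should have one result that answers its question, or a rule for combining several. Here no score within a domain ranks above another. Even the power calculation does not point to one, because its strength figures come from a one-repetition maximum for leg extension, which is not among the listed primary measures.

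If a positive result on any score, or from either of the two performance analyses, can support a statement that a program is effective, two things follow. The 0.05 error rate belongs to one comparison and not to that statement. The choice of which score carries the conclusion also stays open until the data have been seen.

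**Working it through.** **1. Count of primary scores**

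Fitness 2 (steep ramp, endurance); strength 4 (grip, elbow flexion, knee extension, chair stands); MFI 5; FQL 4. Total 2 + 4 + 5 + 4 = 15 scores, from 8 instruments or tests (2 + 4 + 2), in 3 domains.

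**2. Reproducing the sample size**

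Inputs from Power calculation: difference 0.40 SD, power 0.80, two-sided alpha 0.05.

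n per group = 2 × (1.960 + 0.842)² / 0.40² = 98.1, so 99; the t-test version gives 99.1, so 100. The stated 100 is reproduced (power 0.804). It is the size for one test, with no allowance for several primary outcomes. With three tests at 0.05/3 = 0.0167, the same formula gives 2 × (2.394 + 0.842)² / 0.40² = 130.9, so 131 per group.

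**3. Chance of at least one false positive**

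Premise: each test is made at 0.05, no true effect exists, and any one positive result counts. For k independent tests the chance is 1 − 0.95^k.

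| Reading of the planned tests | k | Chance, independent |
|---|---|---|
| One omnibus test per domain | 3 | 14% |
| One omnibus test per instrument | 8 | 34% |
| Each score, one contrast, one visit | 15 | 54% |

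Scores from the same patients are correlated. The documents give no correlations, so I assumed a common value r and evaluated the 15-score case (equicorrelated normal test statistics):

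| r | 0 | 0.3 | 0.5 | 0.7 |
|---|---|---|---|---|
| Chance | 54% | 46% | 36% | 26% |

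The 14% and 34% would also fall with correlation, but they return to 5% only if the tests are perfectly correlated. None of these figures counts the second analysis of the performance outcomes. Testing contrasts and visits separately raises them further.

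**4. Power after narrowing to one score per domain**

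With 360 / 3 = 120 per group (equal groups assumed) and 20% attrition, 96 per group remain. Two-sided t-test, difference 0.40 SD:

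- alpha 0.05: 79%
- alpha 0.0167, the strictest Holm step: 64%

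Adjusting for the baseline value at correlation r with follow-up raises the effective difference to 0.40 / √(1 − r²). At alpha 0.0167:

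| Assumed r | Effective difference | Power |
|---|---|---|
| 0.3 | 0.419 | 69% |
| 0.5 | 0.462 | 78% |
| 0.6 | 0.500 | 85% |
| 0.7 | 0.560 | 93% |

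For fatigue the protocol's own target is 0.50 SD, so the strictest step has 85% power there without adjustment.

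**The case against.** A reader might infer that the plan makes 15 × 3 × 2 = 90 comparisons, each at 0.05, so that a chance success is more likely than not. The document does not support that, for four reasons:

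- Alpha 0.05 appears once, for the sample-size contrast at one visit. No testing level is set for the other comparisons, and no success rule is stated.
- The planned test is a group-by-time MANOVA, not a set of pairwise tests. It could be one omnibus test per instrument or per domain, which gives 34% or 14%.
- The Background expects no difference between the two programs in self-reported outcomes during treatment. That removes 9 fatigue comparisons at T1 and leaves 81. The Power calculation also expects Onco-Move to do little or nothing for strength.
- For 15 scores on one contrast at one visit, the chance exceeds one half only when the scores are close to independent. That is unlikely for five scales of one questionnaire or four strength tests in the same patients.

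The chance would clearly exceed one half if every score, contrast and visit were tested separately: 94%, 87% and 73% at score correlations 0.3, 0.5 and 0.7, with shared arms and an assumed visit correlation of 0.5. The article does not say that this will be done.

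It is also fair that alpha allocation and test order are commonly left to an analysis plan, which is not shown here, so their absence is no fault of the article. That does not remove the point. The primary list and the sample size are both fixed in this article, and they do not match. An analysis plan that adjusted across the published list would be underpowered at the published size: Bonferroni over 15 scores leaves 46% power with 100 per group. One that picked fewer scores would depart from the list.

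**Conclusion.** The concern stands in a limited form. Fifteen scores share primary rank, the performance outcomes have two analyses with none deciding, and the sample size is that of one two-sided 0.05 test for one contrast at one visit.

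If success in any one test is enough, the family error exceeds 0.05 on each reading examined. It is about 14% with one omnibus test per domain, 34% with one per instrument, and 26% to 54% for 15 separate scores on one contrast at one visit (correlation 0.7 down to 0). The first two figures assume independence; the range for 15 scores rests on assumed common correlations. A rule requiring success in all three domains would not inflate the error, but the article states no such rule and the sample size does not allow for one.

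This should be fixed. It concerns how the conclusion is fixed in advance, and it does not show that a false conclusion is likely.

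**What to change.** Before outcome data are examined, amend the protocol and analysis plan as follows:

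1. Name one confirmatory score per domain from those already collected. The choice is the sponsor's; for fitness, the Discussion's remark on the clinical relevance of cycle endurance time may favour that score.
2. Name one deciding analysis for the performance outcomes and label the other as supportive.
3. Make OnTrack against usual care at T1, which the protocol already powers, the confirmatory contrast. Test the three scores by Holm or in a fixed order.
4. Test the other two contrasts afterwards in a stated order, and label the remaining scores and the T2 comparisons secondary.

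No new data are needed. The cost is that some instruments lose primary status, and so do the hypotheses placed at T2. Under Holm, the strictest step has 64% power for 0.40 SD with 96 per group, or 69% to 93% with baseline adjustment at assumed correlations of 0.3 to 0.7. A fixed order keeps the first test at 0.05 (about 79% unadjusted), but formal testing stops at the first score that fails.

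### 100 per group for 0.40 SD reproduces, but 360 with 20% attrition leaves 96 per group, and 0.40 SD does not follow from the expected changes quoted

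*Protocol article*

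**What the plan says.** All of this is in the Power calculation section of the protocol article.

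- **Expected changes.** Usual-care patients "will experience a 5%-10% decline in physical fitness during their chemotherapy treatment". It is hypothesized that "the OnTrack program will yield at least a 20% improvement in general physical fitness".
- **Planning mean and SD.** The only ones given are for one-repetition-maximum leg extension before treatment, taken from an earlier trial: 25 kg and 12 kg.
- **Sample size.** "Based on the above figures, 100 patients per group are needed to detect a 0.40 standard deviation difference". The comparison is "between the OnTrack group and the usual care group at the post-chemotherapy assessment", with power 0.80 and two-sided alpha 0.05.
- **Attrition.** "We will recruit 360 patients into the trial to allow for an attrition of approximately 20"%. Attrition is described as leaving the trial entirely, and includes missed follow-up assessments.
- **Fatigue.** The same numbers are said to be enough for a difference of half a standard deviation.

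The Recruitment and randomization section describes minimization to three groups and does not write out the ratio.

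**The concern.** The section runs as a chain: expected changes lead to 0.40 SD, 0.40 SD leads to 100 per group, and 100 per group leads to 360 after an attrition allowance. The first and third links do not hold.

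The total of 360 looks like 300 increased by a fifth. Losing a fifth of 360 does not lead back to 300. The sentence that introduces 0.40 SD presents it as a result of the figures before it, but those figures give a larger difference.

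At stake are two statements that readers will rely on: how much loss the trial can absorb before it falls below its own requirement, and whether 0.40 SD is the effect expected or a smaller effect chosen for safety. The second affects how a null result would be read.

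**Working it through.** **Inputs** (Power calculation section): 360 recruited; attrition 20%; 100 per group; 0.40 SD; power 0.80; two-sided alpha 0.05; usual care -5% to -10%; OnTrack at least +20%; mean 25 kg; SD 12 kg; fatigue difference 0.50 SD.

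**Assumptions:** equal allocation, so 360/3 = 120 per group; the 12 kg baseline SD also serves as the SD of the post-chemotherapy score; the percentages, stated for general physical fitness, are applied to the leg-extension mean.

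**1. The plan's own figure**

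Normal approximation: n = 2 × (1.960 + 0.842)² / 0.40² = 98.1, so 99 per group. Two-sample t-test: 99.1, so 100 per group. The stated 100 reproduces.

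**2. From 100 per group to 360**

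- What 360 leaves: 120 × (1 - 0.20) = 96 per group, 288 in total.
- What 100 needs: 100 / (1 - 0.20) = 125 per group, 375 in total.
- How 360 arises: 3 × 100 × 1.20 = 360. The requirement was multiplied by 1.20 where it should be divided by 0.80.
- What 360 tolerates: 1 - 100/120 = 16.7%.

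Rounding does not explain the gap. Starting from 99 gives 99/0.80 = 123.75, so 124 per group and 372 in total. Starting from the unrounded 98.1 gives 3 × 98.1/0.80, about 368.

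**3. What 96 per group costs**

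| Quantity at 96 per group | t-test | normal approximation |
|---|---|---|
| Power for 0.40 SD | 0.787 | 0.791 |
| Power for 0.50 SD (fatigue) | 0.931 | 0.934 |

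The difference detectable with 80% power is 0.406 SD (t-test). At 100 per group, t-test power for 0.40 SD is 0.804, so the loss is 1 to 2 percentage points. The fatigue statement holds.

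**4. From the expected changes to 0.40 SD**

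Standardised difference = (OnTrack gain + usual-care decline) × 25 / 12. The n per group is from the t-test; power at 96 is from the normal approximation.

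| Usual-care decline | Difference | In SD units | n per group | Power at 96 per group |
|---|---|---|---|---|
| 10% | 0.30 × 25 = 7.5 kg | 0.625 | 42 | 0.99 |
| 5% | 0.25 × 25 = 6.25 kg | 0.521 | 59 | 0.95 |
| 0% (not what the section expects) | 0.20 × 25 = 5.0 kg | 0.417 | 92 | 0.82 |

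In reverse, 0.40 SD is 0.40 × 12 = 4.8 kg, and 4.8/25 = 19%. The section expects a separation of 25% to 30%. The implied effect is 0.521/0.40 = 1.30 to 0.625/0.40 = 1.56 times the one stated. Because the OnTrack gain is given as a minimum, 0.52 SD is the floor. The value 0.40 is approached only by leaving out the usual-care decline, and even then it is not reached exactly.

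**The case against.** The case for leaving the text alone has several parts.

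**The central calculation is right.** This stands. A reader might infer that the whole paragraph fails; it does not. The 100 per group for 0.40 SD and the fatigue statement both check out.

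**Attrition is only approximate, and may not all fall before the powered assessment.** The power statement concerns the post-chemotherapy assessment, while attrition as defined includes missed follow-up, and the Study outcomes section has a later assessment at six months. Patients lost between the two would still contribute to the powered comparison, and the multilevel regression in the Statistical analyses section can use incomplete series. This stands as a limit: 79% applies only if the full 20% is lost by the end of chemotherapy. It does not rescue the sentence as written, because an allowance of about 17% is what 360 provides and 20% is what is claimed.

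**The effect-size mismatch is on the safe side.** This stands. If the stated changes occur, 96 per group gives power of 0.95 to 0.99. A reader might infer that the trial is underpowered; the document's figures do not support that, and the two discrepancies pull in opposite directions. What remains is that a derivation is claimed and does not follow.

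**The target difference is stated.** This stands. A reader might infer that one cannot tell what the trial was built to detect, but the section gives the size, the outcomes, the comparison, the time point, the power and the alpha.

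**The leg-extension figures are only a planning proxy.** This also stands. It is tempting to call them an error because the one-repetition maximum is not a trial outcome. But knee-extension strength by dynamometer is a primary measure, and the target is in SD units, so 100 per group does not depend on the kilogram scale.

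**Conclusion.** The concern holds in limited form: one stated allowance and one stated derivation are wrong, and neither calls the design into question.

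- **Attrition.** With equal allocation, 360 keeps 100 per group up to 16.7% loss, not 20%. At 20% loss 96 remain. If all of that loss has occurred by the post-chemotherapy assessment, power for 0.40 SD is about 79% and 80% power corresponds to 0.41 SD. This is a small shortfall, and smaller still if some of the loss comes later.
- **Effect size.** The expected changes imply 0.52 to 0.63 SD, needing about 42 to 59 per group, not 0.40 SD and 100. This rests on using the baseline SD as the outcome SD and on applying the fitness percentages to the leg-extension mean; the section supplies no other mean or SD. The error is in the conservative direction.

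**What to change.** Two sentences change; no patients are added and no analysis is altered.

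1. Keep 360 and state either that it allows for about 17% attrition while retaining 100 per group, or that 20% attrition would leave 96 per group, with 79% power for 0.40 SD (80% for 0.41 SD). Recruiting 375 would also reconcile the figures, but for so small a gain in power it is not needed.
2. Replace the opening words that derive 0.40 SD from the preceding figures. Say that 0.40 SD is a chosen, conservative target, below the 0.52 to 0.63 SD implied by the expected changes on the quoted leg-extension scale.

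The only cost is that the attrition allowance, or the stated power, becomes slightly less favourable.

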### Statistical analyses

All primary statistical analyses will be conducted on an intention-to-treat basis. Between group differences over time in performance indicators of general physical condition and muscle strength will be evaluated using multilevel regression analysis for % change from baseline, and two factor (group × time) multivariate analysis of variance with repeated measures on the time factor for comparison of mean scores. Scores on the self-report measures of fatigue, mood state and HRQoL will be calculated according to published scoring algorithms. Between-group differences over time in mean scores will be tested using a two factor (group × time) multivariate analysis of variance with repeated measures on the time factor. Effect sizes will be calculated using standard statistical procedures.

Supplementary analyses will be carried out in which data relating to compliance with the program elements are taken into account. Specifically, we will determine whether the level of compliance (based on attendance records and self-report data) is associated significantly with the changes over time in physical condition, muscle strength, fatigue, mood, and HRQoL. Similarly, we will investigate whether program effectiveness varies significantly as a function of patients' background characteristics, and particularly those variables assessing life style, health behavior and health attitudes.

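### Fitness and strength are tested both as percent change from baseline and as mean scores; one baseline-adjusted analysis would be seldom less, and often more, efficient and easier to interpret

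*Protocol article*

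**What the plan says.** The Statistical analyses section assigns two inferential analyses to the performance outcomes. One is "multilevel regression analysis for % change from baseline". The other is a repeated-measures MANOVA (group by time) of mean scores. No order of precedence is stated.

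The Power calculation section works in SD units: "100 patients per group are needed to detect a 0.40 standard deviation difference", for the contrast "between the OnTrack group and the usual care group at the post-chemotherapy assessment". Its only spread figure is that "a pretreatment mean for the 1-repetition maximum for leg extension is estimated to be 25 kg, with a standard deviation of 12 kg". Its expectations, however, are in percent: "patients in the usual care condition will experience a 5%-10% decline in physical fitness during their chemotherapy treatment", and "the OnTrack program will yield at least a 20% improvement in general physical fitness".

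Under Muscle strength, the listed tests are grip and hand-held dynamometry and chair stands. Leg-extension 1RM is not an outcome. For the cycle endurance test the article sets a ceiling, "with a maximum time of 30 minutes".

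**The concern.** Percent change divides each follow-up value by that patient's own baseline, which contains measurement error and short-term variation. Two things follow.

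- **Precision.** Patients with low baselines produce very large positive ratios. These widen and skew the distribution, so a few weak patients can dominate the comparison.
- **Location.** The mean of individual ratios exceeds the ratio of the means. A group that has not changed on average therefore shows an average percent gain.

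The first costs power on primary outcomes. The second distorts the within-arm figures that the plan uses to express its expectations. Because a mean-score analysis runs in parallel, the two results can also disagree, and the article does not say which one stands.

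**Working it through.** **Inputs from the article.** 0.40 SD; 100 per group; 80% power; two-sided 5% level; 360 patients in three arms; about 20% attrition; baseline mean 25 kg and SD 12 kg.

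From these:
- evaluable per group, if allocation is equal: 360/3 × 0.8 = 96
- CV: 12/25 = 0.48
- effect: 0.40 × 12 = 4.8 kg, or 4.8/25 = 19.2% of the mean

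**Inputs not in the article, so assumed.** Baseline/follow-up correlation ρ (0.5, 0.7, 0.9), shape of the baseline distribution, and transfer of the 1RM spread to the tests actually used. CV 0.20 serves as an alternative.

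**1. The plan's own figure.** n = 2(1.96 + 0.842)²/0.40² = 98.1, so 99 per group. The exact t calculation gives power 0.800 at 99 and 0.804 at 100. The stated 100 is reproduced, but for an unadjusted comparison of raw means. The article gives no SD of percent change, so this sample size says nothing about power on that scale.

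**2. Upward drift.** Take a lognormal baseline and the same mean and SD at follow-up. The expected mean percent change in an unchanged group is (1 + CV²)/(1 + ρCV²) − 1.

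| CV | ρ | Calculation | Mean percent change |
|---|---|---|---|
| 0.48 | 0.5 | 1.2304/1.1152 | +10.3% |
| 0.48 | 0.7 | 1.2304/1.1613 | +6.0% |
| 0.48 | 0.9 | 1.2304/1.2074 | +1.9% |
| 0.20 | 0.5 | 1.04/1.02 | +2.0% |
| 0.20 | 0.9 | 1.04/1.036 | +0.4% |

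Lognormal is the mild case. A normal baseline truncated at 1 kg gives about +26%, +15% and +5% at ρ = 0.5, 0.7 and 0.9. Over all shapes tried, the range is about +2% to +30% at CV 0.48 and +0.4% to +2.4% at CV 0.20.

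A true usual-care decline of 7.5% (the midpoint of 5%-10%) would on average appear, in the lognormal case, as 0.925 × 1.1033 − 1 = +2.1% at ρ = 0.5 and 0.925 × 1.0595 − 1 = −2.0% at ρ = 0.7.

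**3. Raw-scale power, 96 per group, ρ = 0.5.**
- Change score: its SD is σ√(2(1 − ρ)) = σ, so the effect stays 0.40 and power is 0.79.
- ANCOVA: the residual SD is σ√(1 − ρ²) = 0.866σ, so the effect is 0.40/0.866 = 0.462. Then 0.462 × √48 = 3.20, and Φ(3.20 − 1.96) = 0.89.

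**4. Percent-change power.** This needs simulation. Each cell shows percent change / ANCOVA on the raw score, with 100 per arm.

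| Baseline shape (mean 25, SD 12) | +4.8 kg, ρ = 0.5 | +4.8 kg, ρ = 0.7 | ×1.192, ρ = 0.5 |
|---|---|---|---|
| Normal truncated at 1 kg | 40% / 91% | 72% / 98% | 29% / 81% |
| Normal truncated at 3 kg | 58% / 91% | 86% / 98% | 46% / 83% |
| Normal truncated at 5 kg | 68% / 91% | 92% / 97% | 52% / 83% |
| Gamma | 71% / 90% | 96% / 98% | 62% / 84% |
| Lognormal | 86% / 90% | 99% / 98% | 75% / 83% |

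At ρ = 0.9 with the additive effect, both exceed 99% in every shape in the table.

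With 96 per group, the additive effect and ρ = 0.5, the ranges over shapes are 32%-84% for percent change, 76%-82% for the raw change score and 87%-91% for ANCOVA.

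A hand check of the worst cell (truncated at 1 kg, ×1.192): the control SD of percent change is 117.8 points and the mean ratio 1.257. The effect is 0.192 × 125.7 = 24.1 points. The treated SD is 1.192 × 117.8 = 140.4, and the root-mean-square SD is 129.6. The standardized effect is 24.1/129.6 = 0.186 instead of 0.40. Then 0.186 × √50 = 1.32, and Φ(1.32 − 1.96) = 0.26, close to the simulated 29%.

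**5. Error rate.** With no treatment effect, the percent-change test rejected in 3.6% to 5.8% of simulated trials.

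**The case against.** The case for leaving the plan alone has real substance.

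- **Percent change is not the only analysis.** The planned mean-score analysis keeps roughly the intended power (76%-82% at ρ = 0.5). A rule of precedence may sit in an analysis plan that is not shown. This stands, and it removes any claim that the primary outcomes depend on percent change alone.
- **The loss is not implied by the plan's figures.** A reader might infer that the stated mean and SD by themselves cost the trial much of its power. They do not: shape and correlation are also needed, and the article gives neither. The lowest values come from near-normal baselines with a few patients near zero.
- **The spread belongs to another test.** At CV 0.20 and ρ = 0.5, percent change has about 75%-80% power, close to the raw change score. What remains against ANCOVA (89%) is largely the deficit of any change score.
- **The hypothesised contrast is larger than 0.40 SD.** Taken as −7.5% against +20%, it left percent change with 78%-98% power at ρ = 0.5 in the lognormal, gamma and higher-truncation (3 or 5 kg) shapes.
- **The drift does not create false positives.** A reader might infer a biased treatment comparison. With no effect, the drift arises equally in all randomised arms, and the error rate stays near 5%.
- **The endurance ceiling is not specific to percent change.** It limits the possible gain to (30 − b)/b, which is +900% from b = 3 minutes and +50% from b = 20. Those baselines are illustrative, and the ceiling truncates raw times too.

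The percent scale also matches how the article states its expectations, which is a good reason to report it. It is not a reason to test on it.

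**Conclusion.** The point holds as a matter of efficiency and interpretation. Percent change beat the baseline-adjusted analysis only marginally and in few settings (99% against 98% with a lognormal baseline at ρ = 0.7), and it was often well behind. The gap at ρ = 0.5 runs from a few points to more than 50, and it closes at a correlation near 0.9. Its size rests on an assumed CV, shape and correlation, so no single figure for lost power can be attributed to this trial.

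The upward drift is certain in direction. Its size ranges from under 1% to about 30%, depending on the same assumptions. It matters for statements such as whether usual care declined, not for the validity of the randomised comparison. The documents support neither an inflated error rate nor a trial-wide power failure, so this is a worthwhile, low-cost improvement and not a must-fix.

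**What to change.** For each performance outcome, name one inferential analysis: the multilevel model already planned, with the follow-up values (end of chemotherapy and six months) as the dependent variable and the baseline value as covariate. Use the raw scale, or the log scale for clearly skewed outcomes.

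Remove percent change as a tested outcome. Report it descriptively, derived from the adjusted means relative to the baseline mean, which avoids averaging individual ratios. As an optional refinement, treat endurance times that reach 30 minutes as right-censored.

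The cost is wording only. The article has baseline measured before randomisation, so no new data, visits or patients are needed. The one downside is that the percent-change result becomes descriptive.
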